**6. SPECIFIC AIMS**

**Primary Aim 1:** Evaluate the feasibility and acceptability of ROC and CBT.

**Primary Aim 2:** Compare the efficacy of ROC and CBT on binge eating over the duration of the study.

**Primary Aim 3:** Compare the efficacy of ROC and CBT on weight loss (BMI) and energy intake (as measured by 24-hour dietary recalls) over the duration of the study.

**Secondary Aim 1:** Determine the extent to which ROC and CBT influence underlying mechanisms of action, including responsivity to food cues, satiety responsiveness, and reward-based eating.

**Exploratory Aim 1:** To evaluate moderators of treatment (age, gender, binge eating status, satiety responsiveness, responsivity to food cues, reward-based eating) and mediators of treatment outcomes (responsivity to food cues, satiety responsiveness, reward-based eating, physical activity).

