## **Research Design and Methods**

**Study Overview.** This proposal is a randomized controlled study with two arms: ROC and CBT. The ROC program targets improved satiety responsiveness and decreased food responsiveness and provides psychoeducation (ways the environment “tricks” the body into overeating past nutritional needs, coping skills designed to assist in mastery and toleration of food cue sensitivity, daily self-monitoring (hunger, satiety, and cravings)) and experiential learning (exposure sessions while self-monitoring hunger, satiety, and cravings). Additionally, the ROC participants will be taught to decrease caloric intake and increase physical activity, to assist with satiety responsiveness and to decrease food cue responsiveness. The CBT treatment program focuses on disrupting the restraint/binge cycle by improving maladaptive thoughts surrounding eating, shape, and weight. As part of CBT, participants self-monitor food intake, to understand the thoughts that trigger binge eating and as a way to identify times of restriction that can trigger binge eating. CBT targets explicit urges to binge eat but does not include experiential exercises. (See Table 1)

We will recruit 300 overweight and obese male and female Veterans with BED or subclinical BED to randomize at least 120 meeting all inclusion criteria, will provide 5 months of treatment and will follow participants for 6 -months post-treatment. Total length of participation will be approximately 11 months. Participants will complete assessments at baseline, mid-treatment (~week 10), post-treatment (week 20), and 6-month follow-up (week 44). Participants will complete brief survey assessments monthly during treatment to assess mediators. We will also collect data on feasibility and acceptability of the two treatments. In person assessments will take 3-4 hours except for the mid treatment which will be about 1 hour. This study is being conducted in collaboration with investigators from the VA San Diego Healthcare System (VASDHS). The collaborators will file a separate IRB proposal through the VA to cover their research activities which will include directly recruiting Veterans from health clinics at the VA and conducting the initial screen. Information collected in their screen will securely be shared with our research team. UCSD team will complete the remainder of screening, assessments and treatment of the participants.

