| Physical activity prescription | Physical activity is used to help regulate physiological and psychological responding to food cues.                                                                                                                                                                          | None                                                                                  |
| Goal setting                   | Goal setting focuses on self-monitoring and practicing mastery and toleration of physiological /psychological arousal, as well as food intake and physical activity                                                                                                          | Goal setting focuses on self-monitoring of food intake, thoughts and behaviors.       |
| Coping skills                  | Methods for managing psychological and physiological arousal. Discussed each week in regards to mastery and toleration of physiological /psychological arousal.                                                                                                              | Cognitive restructuring, stress management, behavior chains to reduce binge eating    |

(total treatment duration = 5 months, 18 meetings). Descriptions of the treatment arms follow and key differences between the treatment arms are outlined in Table 1. All treatment sessions will be audiorecorded for supervision and fidelity purposes.

**Regulation of Cues (ROC).** The ROC program provides psychoeducation, coping skills, self-monitoring and experiential learning. Physical activity will be promoted to improve self-regulatory strength and to help participants master and tolerate physiological and psychological arousal, resist cravings and overeating.

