**Exploratory Aim 1:** This aim will evaluate whether 1) individual factors including baseline age, gender, binge eating status, satiety responsiveness, responsivity to food cues, or reward-based eating moderate the impact of ROC vs CBT on improvements in binge eating and weight by evaluating two interaction terms in primary outcome models, and whether 2) improvements in responsivity to food cues, satiety responsiveness, reward-based eating or physical activity mediate improvements in binge eating and weight, by screening each in single mediator models prior to estimating joint effects food cue responsiveness, satiety responsiveness, or reward-based eating mediate improvements in binge eating, using a multiple mediator model. Significance tests of indirect effects will be assessed using a product of coefficients method with bootstrap estimation of 95% confidence intervals.

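### The joint mediator model for Exploratory Aim 1 leaves out physical activity and the weight outcome, so part of an activity effect could be credited to cue, satiety or reward mechanisms

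*Protocol*

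**What the plan says.** Section 6 of the protocol (Specific Aims, Exploratory Aim 1) lists "mediators of treatment outcomes (responsivity to food cues, satiety responsiveness, reward-based eating, physical activity").

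The Analyses Plan, Exploratory Aim 1, repeats all four and gives two outcomes. It asks whether improvements in the mediators, ending with "reward-based eating or physical activity mediate improvements in binge eating and weight, by screening each in single mediator models", carry the effect. It then moves to a joint analysis, "prior to estimating joint effects food cue responsiveness, satiety responsiveness, or reward-based eating", to see whether these "mediate improvements in binge eating, using a multiple mediator model". Activity is absent from that list, and weight is absent as an outcome. The test is stated next: "Significance tests of indirect effects will be assessed using a product of coefficients method with bootstrap estimation of 95% confidence intervals".

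On activity itself, Table 1 (Treatment Arms) gives CBT no activity prescription and says of ROC: "Physical activity is used to help regulate physiological and psychological responding to food cues". The Study Overview under Research Design and Methods adds that ROC participants are taught to "increase physical activity, to assist with satiety responsiveness and to decrease food cue responsiveness".

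**The concern.** A multiple-mediator model is used to separate mediators that move together. Single-mediator models cannot do this, because each credits its mediator with whatever it shares with the others. The joint model is therefore the one planned analysis that could tell activity apart from cue, satiety and reward mechanisms, and as written activity is not in it.

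Activity is also not an arbitrary omission. Its prescription differs by arm by design, and the protocol expects it to be related to the mediators that stay in. If it also reaches the outcome by a path that bypasses them, leaving it out biases the mediator-to-outcome coefficients, and so the indirect effects. A direct path is easy to imagine for weight, and for weight no joint model is written at all.

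What is at stake is the mechanistic reading of the trial, not its efficacy result: an indirect effect could be reported for a mediator that did nothing.

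**Working it through.** The protocol gives no effect size, power or error rate for the mediation analysis, so there is no figure to reproduce. The check compares the text with itself and then sizes the consequence under stated assumptions.

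**1. The text side by side**

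| Place | Mediators | Outcomes |
|---|---|---|
| Specific Aims | cue, satiety, reward, activity | treatment outcomes |
| Analyses Plan, single-mediator stage | cue, satiety, reward, activity | binge eating and weight |
| Analyses Plan, joint model | cue, satiety, reward | binge eating |

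**2. Size of the false indirect effect**

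Inputs: N = 120 is from the protocol; 1:1 allocation is assumed. All paths are assumptions, in SD units:
- ROC effect on activity: 0.5
- activity effect on the outcome, direct: b = 0.4
- ROC effect on each retained mediator: a = 0.5
- effect of each retained mediator on the outcome: 0
- residual correlation r among all four mediators: 0 to 0.5

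The true indirect effect through activity is 0.5 × 0.4 = 0.20.

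With activity omitted, each of the three retained mediators picks up a coefficient b × r/(1 + 2r). The summed false indirect effect is 3 × a × b × r/(1 + 2r):
- r = 0.2: 3 × 0.5 × 0.4 × 0.2/1.4 = 0.086
- r = 0.3: 3 × 0.5 × 0.4 × 0.3/1.6 = 0.113
- r = 0.5: 3 × 0.5 × 0.4 × 0.5/2.0 = 0.150

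At r = 0.5 this equals 0.15/0.20, or three quarters of activity's own indirect effect. Simulation gave 0.087, 0.112 and 0.150, in agreement. With activity in the model the sum is about 0.

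**3. How often an inert mediator is declared**

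Simulation with 1,500 trials per setting and linear models; simulated 95% limits for the product of coefficients stand in for the bootstrap. The figure is the chance that at least one of the three inert mediators has an interval excluding zero.

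| r | Without activity | With activity |
|---|---|---|
| 0 | 11% | 11% |
| 0.2 | 18% | 10% |
| 0.3 | 23% | 10% |
| 0.5 | 28% (about 30% in a separate run) | 9% |

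The level of about 10% is ordinary multiplicity over three intervals, not bias. With 96 analysed (an assumed 20% loss), the figures at r = 0.2, 0.3 and 0.5 are 14%, 14% and 20% without activity, and 9%, 7% and 9% with it.

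**4. Where the problem disappears**
- r = 0: 11% either way.
- Direct activity path zero (r = 0.3): 9% without activity and about 9% with it.
- ROC does not move the retained mediators (r = 0.3): 1% without activity.

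**5. Imperfect measurement of activity**

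The Godin questionnaire is a self-report of weekly exercise occasions. In a simpler setting with one retained mediator (arm effects 0.5, activity path 0.3, r = 0.5), the false-declaration rate is 25% without activity and 3% with activity measured without error. At an assumed reliability of 0.5–0.7 it is 6–12%.

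**The case against.** The strongest reply is that the bias is conditional. The protocol's stated rationale has activity working through satiety and cue responsiveness. To that extent, crediting those mediators is correct. This stands: with no direct activity path there is no bias, and the documents give no value for any path. Much larger rates can be produced: 69% in a one-mediator setting with 0.8 SD arm effects, path 0.5 and correlation 0.5. That is an extreme case and should not be quoted as typical.

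Second, a reader might infer that mediators are selected by significance on the same data, so that the joint intervals are also selective. The documents do not support this. The protocol says "by screening each in single mediator models prior to estimating joint effects" but gives no criterion; its mention of significance concerns the indirect effects. If the joint model is fixed at the three listed mediators, screening selects nothing. If screening does decide entry, activity is among those screened and might enter. Were a 5% screen applied to the three retained mediators with activity left out, the rates above would rise to 22%, 34% and 48% at r = 0.2, 0.3 and 0.5, but that rule is not in the text. Omission alone creates the bias.

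Third, the sentence is visibly garbled, so the omission may be a drafting slip, and detail could sit in an analysis plan not shown here. That is fair as to intent. However, this is a stated model that falls short of its own aim, not a detail left open.

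Fourth, activity is not hidden: it is tested as a single mediator for both outcomes. ROC also contains reduced caloric intake and coping skills, which no joint model of these four mediators would separate. Both points stand and limit what the fix can deliver.

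**Conclusion.** The mismatch is in the text and does not depend on any assumption: four mediators and two outcomes are announced, and the joint model is written for three mediators and one outcome, with no reason given. The consequence does depend on assumptions. It requires a direct activity effect on the outcome, residual correlation between activity and the retained mediators, and a ROC effect on those mediators. With arm effects of 0.5 SD, an activity path of 0.4 and N = 120, about 18–30% of trials would declare at least one inert mediator at correlations of 0.2–0.5, against about 10% with activity included.

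A reader might go further and conclude that the trial's central claim is at risk. The protocol does not support that. Its primary aims are feasibility and acceptability, binge eating, and weight with energy intake; mediation is exploratory. No primary or secondary result changes. The correction is worth making because it is cheap and uses data already scheduled.

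**What to change.** Reword the Analyses Plan, Exploratory Aim 1, so that one multiple-mediator model contains food cue responsivity, satiety responsiveness, reward-based eating and physical activity, fitted once for binge eating and once for BMI. State that entry into this model is not decided by the single-mediator results, which are reported as descriptive. If activity or weight is left out on purpose, give the reason.

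The cost is about one sentence and slightly wider intervals from one more mediator. No new data are needed, since the Godin questionnaire and weight are already collected at baseline, mid-treatment, post-treatment and follow-up. The report should add that, because activity is self-reported, including it reduces the misattribution but does not fully remove it.

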## 10. HUMAN SUBJECTS

Overall, we expect to consent 300 individuals to randomize and have at least 120 Veterans and civilians (if needed) start treatment who meet the following eligibility criteria:

Enrollment criteria:

1. All participants will be Veteran or civilian men and women between the ages of 18-65 meeting criteria for overweight, with a BMI  $\geq 25$ .
2. Participants will meet Diagnostic and Statistical Manual–5 (DSM-5) criteria for BED or subclinical BED
3. Participants will be willing and able to participate in assessment visits and treatment sessions at University of California, San Diego (UCSD).
4. Participants will be able to provide data in English through interviews and questionnaires and understand treatment materials in English.
5. Participants will be willing to maintain contact with the investigators for 11 months.
6. Participants will be free of serious or unstable medical (current symptoms of angina, stroke, heart disease or other serious medical condition that would make physical activity unsafe or impossible at a moderate level) or psychiatric illness (i.e., active suicidal ideation, history of suicide attempt within 1 year, current unmanaged psychosis, manic episode, anorexia nervosa, bulimia nervosa, or substance abuse within the past year) or psychosocial instability (e.g., homelessness) that could compromise study participation.
7. Participants will be free from conditions in which exercise or weight loss will be detrimental to the participant's health (e.g., pregnancy); pharmacotherapy for obesity or binge eating disorder (e.g., Orlistat or Meridia) or bariatric surgery within the past 6 months or planning to start such treatments in the next 11 months.
8. Participants will not be moving out of the San Diego area for the duration of their study enrollment (11 months).
9. Participants will not be pregnant, planning to get pregnant in the 11-month study period or lactating.
10. Participants will not be taking medication that may impair physical activity tolerance or performance (e.g., beta blockers)
11. Participants will not be participating in group or individual psychotherapy for binge eating or weight management.
12. Participants with medical or psychological problems or taking medications that could make adherence with the study protocol difficult or dangerous will not be included.

## 11. RECRUITMENT AND PROCEDURES PREPARATORY TO RESEARCH

Participants will be recruited from the San Diego Metropolitan community and the VA San Diego Healthcare System (VASDHS). [name] (co-investigator) and her team will recruit Veterans across multiple clinics including weight control, primary care, and mental health clinics. In addition to recruitment through clinics, [name] will recruit Veterans through identifying potential participants through medical records, physician referrals, and electronic and paper flyers. [name] and her team will consent potential participants using the VA consent form which covers these pre-screen activities and will pre-screen Veterans from VASDHS for initial potential eligibility and interest. The brief pre-screening will help screen for inclusion/exclusion criteria and be similar to the online/phone screen used at UCSD.

Upon initial eligibility and interest, the VASDHS team will invite eligible participants to attend an in-person orientation at UCSD and provide the UCSD research team the contact information those who are eligible and UCSD staff will complete all remaining study procedures starting with orientation and UCSD consent. The recruitment efforts of the VA staff will be covered under the VASDHS IRB and participants recruited through this method will be the only participants who sign the VA consent form which will cover [name] and her staff obtaining the information needed to prescreen participants.

Additional efforts will be made to recruit Veterans from the community as well to capture individuals who may not receive their healthcare at the VA and maximize efforts to recruit Veterans for this study. The Center for Healthy Eating and Activity Research (CHEAR) at UCSD recruits through newspaper ads, online advertisements, social media, radio ads, online marketing and physician referrals. In an effort to speed recruitment, CHEAR hired Bump in 2017, a company that provides online recruitment campaigns and software. Bump uses proprietary algorithms developed through machine learning to target profiles for specific participant groups. Bump may advertise on Facebook, Google, Instagram, medical informational sites, and other relevant networks. Every effort will be made to recruit only Veterans for this study. However, should any significant recruitment delays occur, the team will consider the recruitment of active duty service members in the community and civilians if necessary who meet inclusion/exclusion criteria to assure recruitment milestones are met in a timely fashion to complete the trial and have sufficient power.

Veterans who do not complete the prescreening with VASDHS staff, will be asked to complete a brief (~10 minute) secure online survey to screen for inclusion/exclusion criteria (age, self-reported binge eating, BMI, medication exclusions, psychiatric exclusions, pregnancy). If any participants do not wish to complete this online, they could complete it on the phone with a CHEAR staff member along with the phone screen. Those who remain eligible after the online screen, will complete a phone screen with a trained CHEAR staff member to further assess inclusion and exclusion criteria.

All potential participants who remain eligible after the prescreening by VASDHS staff or CHEAR staff will attend a brief orientation at CHEAR, conducted by [name] or CHEAR study staff, which will describe the study, the two treatments arms, randomization methods, expectations for participation, and incentives for time and effort. Following the orientation, those who remain interested, will undergo the UCSD consent process and will sign consent forms, have their height and weight measured, and be scheduled for their first assessment visit. This recruitment and orientation process is used in [name] current and past NIH funded studies and serves to educate potential research participants on randomized controlled trial research process, the current study, and the informed consent process.

## **12. INFORMED CONSENT**

Participants recruited at the VA will sign the VA consent form (covered under the VA IRB) to cover initial screening.

For participants recruited directly through UCSD, a waiver of documented consent is requested for the online screening and phone screening process (UCSD recruited participants only). Prior to baseline visit, the online screening will assess for basic inclusion and exclusionary criteria. This process presents no more than minimal risk of harm to subjects, and involves no procedures, for which written consent is normally required outside of the research context. For individuals who do not have online access or wish to provide the information online, the questions asked on the online screen can be administered over the phone in conjunction with the phone screen. The phone screening will assess for basic inclusion and exclusionary criteria. This process presents no more than minimal risk of harm to participants, and involves no procedures for which written consent is normally required outside of the research context. For these reasons, we request a waiver of documented consent for the phone screen.

All participants, regardless of how they were recruited will complete UCSD written informed consent prior to enrollment at an orientation session. It is not likely that participants for this population will lack the capacity needed for consent. If there are any concerns, to ensure participants understand the consent form, they will be asked to describe what the study is about. For participants in which capacity for consent is judged to be questionable, they will complete the Mini-mental State Examination (MMSE) and if they receive under a score of 24, they will not be

eligible for enrollment (i.e., surrogate consent will not be acceptable). It is highly unlikely that the MMSE will need to be administered to this patient population but if it is administered, documentation of the test results will be kept in the participant file.

The orientation and UCSD consent process may take place with a group of potential participants. Participants may ask questions as a group and they will also be informed that they can each have an opportunity to privately ask additional questions. If individuals are unsure as to whether they are willing to participate in the study, they may take the consent form home with them. If they later decide they wish to participate, they may schedule their first assessment and sign the consent form prior to participating in the assessment.

CHEAR staff members able to provide information about the study and carry out the consent procedures include [name], [name], [name], [name], [name], [name], [name], [name], [name] and [name].

